# Reshaping the path of mild cognitive impairment by refining exercise prescription: a study protocol of a randomized controlled trial to understand the “what,” “for whom,” and “how” of exercise to promote cognitive function

**DOI:** 10.1186/s13063-022-06699-7

**Published:** 2022-09-09

**Keywords:** Randomized controlled trial, Mild cognitive impairment, Aerobic training, Resistance training, Cognition, Mobility, Biomarkers, Exercise

## Abstract

**Background:**

Targeted exercise training is a promising strategy for promoting cognitive function and preventing dementia in older age. Despite the utility of exercise as an intervention, variation still exists in exercise-induced cognitive gains and questions remain regarding the type of training (i.e., what), as well as moderators (i.e., for whom) and mechanisms (i.e., how) of benefit. Both aerobic training (AT) and resistance training (RT) enhance cognitive function in older adults without cognitive impairment; however, the vast majority of trials have focused exclusively on AT. Thus, more research is needed on RT, as well as on the combination of AT and RT, in older adults with mild cognitive impairment (MCI), a prodromal stage of dementia. Therefore, we aim to conduct a 6-month, 2 × 2 factorial randomized controlled trial in older adults with MCI to assess the individual effects of AT and RT, and the combined effect of AT and RT on cognitive function and to determine the possible underlying biological mechanisms.

**Methods:**

Two hundred and sixteen community-dwelling adults, aged 65 to 85 years, with MCI from metropolitan Vancouver will be recruited to participate in this study. Randomization will be stratified by biological sex and participants will be randomly allocated to one of the four experimental groups: (1) 4×/week balance and tone (BAT; i.e., active control); (2) combined 2×/week AT + 2×/week RT; (3) 2×/week AT + 2×/week BAT; or (4) 2×/week RT + 2×/week BAT. The primary outcome is cognitive function as measured by the Alzheimer’s Disease Assessment Scale-Cognitive-Plus. Secondary outcomes include cognitive function, health-related quality of life, physical function, actigraphy measures, questionnaires, and falls. Outcomes will be measured at baseline, 6 months (i.e., trial completion), and 18 months (i.e., 12-month follow-up).

**Discussion:**

Establishing the efficacy of different types and combinations of exercise training to minimize cognitive decline will advance our ability to prescribe exercise as “medicine” to treat MCI and delay the onset and progression of dementia. This trial is extremely timely as cognitive impairment and dementia pose a growing threat to global public health.

**Trial registration:**

ClinicalTrials.gov NCT02737878. Registered on April 14, 2016.

## Introduction

Dementia is one of the most pressing health care issues of the twenty-first century. Individuals with cognitive impairment and dementia have reduced quality of life as they lose their functional independence [1]. As the proportion of the population over 65 years continues to increase, dementia will place increasing demands and costs on the public health system [2]. Thus, the societal value of identifying and developing effective intervention and prevention strategies cannot be overstated [3]. If the onset and progression of dementia were delayed by 1 year, there would be 9 million fewer cases by 2050 [3].

Effective pharmacologic treatment of dementia remains a major challenge [4]. Exercise is a promising strategy for preventing dementia [5]. Notably, exercise significantly reduces key cardiometabolic risk factors for dementia [6, 7], such as hypertension and type 2 diabetes, for both Alzheimer’s disease and vascular cognitive impairment—the two most common types of dementia.

Broadly, there are two distinct forms of exercise: (1) aerobic training (AT; e.g., running), aimed at improving cardiovascular health; and (2) resistance training (RT; e.g., lifting weights), aimed at improving muscle strength. Each type of exercise training has its own distinct physiology and benefits [8]. Evidence from randomized controlled trials (RCTs) suggests that both AT and RT enhance cognitive function in older adults without cognitive impairment and dementia [9, 10]. However, questions regarding the type of training (i.e., what), as well as moderators (i.e., for whom) and mechanisms (i.e., how) of benefit still remain [11, 12].

In regard to what type of exercise, the majority of published RCTs have focused solely on AT [9, 13]. Thus, more research is needed on RT, as well as on the combination of AT and RT. Importantly, to our knowledge, there is no single published high-quality RCT that has examined both the individual and combined effects of AT and RT on cognitive function in older adults. Establishing the efficacy of different types and combinations of exercise training will advance our understanding of how to best prescribe exercise to attenuate cognitive decline. For example, exercise prescription could be personalized according to deficits in specific cognitive domains. For those who do not have the mobility to uptake AT, RT could be recommended as an evidence-based alternative.

For whom exercise benefits, there is good evidence that targeted exercise training improves cognitive function in healthy older adults [9, 10, 14–16]. However, the role of exercise interventions among those at increased risk for dementia, such as older adults with mild cognitive impairment (MCI), is not well established [14, 17–21]. Currently, there is wide recognition that MCI represents the prodromal stage of Alzheimer’s disease, vascular cognitive impairment, and mixed dementia [22–25]. MCI is a clinical entity characterized by cognitive decline greater than that expected for an individual’s age and education level but that does not interfere notably with everyday function [26]. Individuals with MCI are at increased risk for dementia [22]; those with MCI develop Alzheimer’s disease at a rate between 10 and 30% annually [27, 28], whereas those without MCI develop dementia at a rate between 1 and 2% annually [27]. Evidence also suggests that older adults with MCI experience significant declines in quality of life [1, 29]. Thus, older adults with MCI represent an ideal target population for intervention strategies, as the preservation of their cognitive function will likely prolong their ability to live independently and with quality.

Evidence suggests older females may reap greater cognitive gains from AT than older males, particularly in the cognitive domain of executive functions [10, 13, 30–32]. Much of this evidence comes from meta-analyses comparing RCTs of AT that have a high percentage of older females to RCTs with low percentage of older females (i.e., data not disaggregated by biological sex) [13, 33]. Direct RCT evidence is restricted to post hoc analyses [30–32], which are not definitive because statistical power is lacking. Moreover, whether there are sex differences in the effect of RT on cognition is largely unexplored.

Our current understanding of how exercise promotes cognitive function in humans is limited and largely focuses on central induction of neurotrophic factor cascades, such as brain-derived neurotrophic factor (BDNF) and insulin-like growth factor (IGF-1). Evidence from rodent models suggests different types of exercise training may promote cognitive health through divergent pathways, with AT preferentially increasing BDNF and RT preferentially increasing IGF-1 [34]. In humans, AT increases peripheral BDNF levels [35, 36] and, while less studied, RT increases IGF-1 [37, 38].

AT and RT may also promote cognitive function through parallel pathways, including reducing peripheral and central inflammation, which is associated with the pathogenesis of MCI [39]. Indeed some evidence supports the ability of AT and RT to reduce circulating levels of certain inflammatory markers in those with MCI [40].

Gaining insights into the underlying biological mechanisms will enable the refinement of existing exercise recommendations. For example, if RT preferentially increases IGF-1 compared with AT, then RT may be the more appropriate recommendation for individuals with the BDNF Val66met polymorphism, a common single-nucleotide polymorphism resulting in reduced activity-dependent secretion of the mature form of BDNF [41].

Thus, we aim to conduct a 2 × 2 factorial RCT of exercise in community-dwelling older adults with MCI. Our primary objective is to assess the individual effects of AT and RT, as well as the combined (i.e., interaction) effect of the two types of exercise training on cognitive function, as measured by the Alzheimer’s Disease Assessment Scale-Cognitive-Plus (ADAS-Cog-Plus). The secondary objective is to assess sex differences. The tertiary objectives are to explore the mechanisms underlying the individual and interaction effects of AT and RT, and to explore the potential moderation of effects by the BDNF Val66Met polymorphism.

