### Sample size considerations

The planned sample size was determined with the aim of testing the main effects of AT and RT on changes in cognitive function, as assessed by the ADAS-Cog-Plus [50]. In computing the required sample size, we used G*Power and the sample analytic model in the statistical analyses. Unpublished data from a separate set of 96 older adults with MCI from our laboratory estimated that the correlation between baseline ADAS-Cog-Plus and the same measure collected 6 months later was approximately 0.80 [51]. This value was used to calculate the assumed residual variance in the analysis of covariance (ANCOVA) model of 0.36 (i.e., 1 − 0.80^2^). With a targeted enrolment of 216 individuals and accounting for an overall dropout of 15% (assumed to impact each intervention arm equally), we will have a power of 0.80 to detect a standardized mean difference (SMD) of 0.27 for the effect of AT or RT on cognitive function with a two-tailed alpha of 0.05 applied to each comparison [9]. The SMD of 0.27 concurs with findings from recent meta-analyses [9, 52, 53]. To detect an interaction between AT and RT with 0.80 power, the true effect size of 0.53 is required. Figure 2 depicts the 3 planned primary comparisons to examine the main and interaction effects of AT and RT.

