### Statistical analyses

Initial descriptive analyses will compute percentages, mean, or median values for baseline characteristics for each of the treatment arms. Next, missing data will be examined to identify the nature of missing data. Even if data are missing completely at random, missing data will be imputed to improve statistical power using multivariate imputation by chained equations [105]. Forty imputed data sets will be created following 40 iterations of a Gibbs sampler for each imputed data set. Proper convergence of the Gibbs sampler will be confirmed by visual inspection of trace plots of each imputed variable, to ensure proper mixing and the absence of spikes or systematic trends across iterations. Analyses will be pooled across the 40 imputed data sets.

The primary analysis will be performed according to the intention-to-treat principle and entail mixed effects ANCOVA to test the main effects of AT and RT, as well as the interaction effect of AT × RT (see Fig. 2) on changes in cognitive function, as assessed by the ADAS-Cog-Plus. The ANCOVA model will use the repeatedly measured (6-month and 18-month) ADAS-Cog-Plus performance as the dependent variable; baseline ADAS-Cog-Plus score, biological sex, AT, RT, and AT × RT as independent, fixed effects variables. Furthermore, to model changes in the outcome between months 6 and 18, and to estimate distinct treatment effects at months 6 and 18, a fixed main effect of time and all interactions between time and the independent variables will be included. To account for the dependency in the repeatedly measured outcome, a random subject-level intercept will be included. Month 6 will be considered the primary endpoint and month 18 will be considered the secondary endpoint. Secondary analyses of the primary outcome will examine the interaction between biological sex and effects of AT, RT, and AT × RT. A two-tailed alpha of 0.05 will be used for each comparison (i.e., uncorrected alpha).

Secondary outcomes will be examined using identical random-effects ANCOVA models as those constructed with the primary outcome.

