## Discussion

We have assembled a unified, transdisciplinary, and experienced team to use a multi-pronged approach to assess the individual effects of AT and RT, as well as the interaction effect of combining the two types of exercise training on cognitive function and determine the possible underlying biological mechanisms in older adults with MCI. We expect that at the end of the 6-month intervention, compared with BAT, both AT and RT will demonstrate improved performance on the ADAS-Cog-Plus, in specific cognitive domains (i.e., executive functions and episodic memory), and in health-related quality of life, with the greatest improvements seen in the combined AT and RT group. We also hypothesize that the effects of AT and RT will be moderated by biological sex and genotype with greater AT benefits seen in females and those without the BDNF Val66Met polymorphism and greater RT benefits seen in males and in BDNF Val66Met polymorphism carriers.

Our study has some limitations that should be taken into consideration. Given our selection criteria, we will include older adults with MCI due to Alzheimer’s disease, vascular cognitive impairment, or both. Thus, our sample will be heterogeneous; however, this will increase the generalizability of our results. Despite the rigorous cognitive assessments included in our study, to ultimately appreciate the role of exercise in dementia prevention, studies that follow dementia progression rates are needed. Our study will provide critical data for future intervention trials powered to assess dementia progression rates as their primary outcome. We were unable to assess the sample size requirements for each of our secondary or tertiary outcomes. Thus, some of these outcomes will be underpowered.

This 2×2 RCT addresses the problem of how to effectively minimize cognitive decline among older adults with MCI—a population at increased risk for dementia—with different types of exercise. Establishing the efficacy of different types and combinations of exercise training will advance our understanding of how to best prescribe exercise to attenuate cognitive decline. Ultimately, our study results will allow decision makers to leverage the financial support needed for readily accessible and tailored community-based interventions to promote cognitive health and combat dementia.

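### The primary objective labels the AT × RT interaction as the combined effect, so no primary comparison directly tests whether the AT+RT arm improves most

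*Protocol article*

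**What the plan says.** All references are to the protocol article.

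- **Introduction (objectives).** The primary objective covers the individual effects of AT and RT and "the combined (i.e., interaction) effect of the two types of exercise training on cognitive function". The words in parentheses act as a definition.
- **Abstract, Background.** The aim is given as the individual effects and "the combined effect of AT and RT on cognitive function", with no mention of interaction.
- **Sample size considerations.** Fig. 2 (not shown in the text at hand) is said to depict "the 3 planned primary comparisons to examine the main and interaction effects of AT and RT". Power is stated as 0.80 for an SMD of 0.27 for AT or RT, and an interaction of 0.53 is said to be needed for 0.80 power.
- **Statistical analyses.** The primary analysis is a "mixed effects ANCOVA to test the main effects of AT and RT, as well as the interaction effect of AT × RT". On timing, "Month 6 will be considered the primary endpoint". Alpha is 0.05 two-sided for each comparison, uncorrected.
- **Discussion.** The authors expect that, at the end of the intervention, "compared with BAT, both AT and RT will demonstrate improved performance on the ADAS-Cog-Plus", and they add "with the greatest improvements seen in the combined AT and RT group".
- **Economic evaluation.** This is the only place that plans to compare each exercise arm with BAT and to rank the arms, and it does so for cost-utility, not for cognition.

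**The concern.** Combined effect has two meanings here. One is what a person gains from doing both types of training: AT+RT against BAT, or against either type alone. The other is the interaction: whether AT does more, or less, when RT is also given. The objective treats the two as the same, and the primary comparisons follow the second. The Discussion's expectation is of the first kind.

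The stake is interpretation. If AT and RT simply add, the AT+RT arm gains most and the interaction is zero. Under the objective's own label, that result is a null combined effect. If the benefits overlap partly, the labelled effect takes the opposite sign even though the AT+RT arm is still best. The trial is meant to inform which type or combination of exercise to prescribe, so the label matters.

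**Working it through.** **Inputs.** From Sample size considerations: 216 enrolled, 15% dropout, residual variance 0.36 (SD 0.60), SMD 0.27 per main effect, alpha 0.05 two-sided. From Randomization: 1:1:1:1. Completers: 216 × 0.85 = 183.6, taken as 184, or 46 per arm. Effects are in SD units, signed so that positive means improvement (lower ADAS-Cog-Plus scores are better). BAT is set to 0.

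**The plan's own figures.**
- Main effect: SE = 2 × 0.60/√184 = 0.088. At 0.27, z = 3.05 and power = Φ(3.05 − 1.96) = 0.86, against 0.80 stated. Detectable at 0.80: 2.80 × 0.088 = 0.248.
- Interaction: SE = 4 × 0.60/√184 = 0.177. At 0.53, power is 0.85. Detectable at 0.80: 0.496.

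The stated inputs therefore give somewhat more power than claimed. The mismatch is conservative and does not bear on this point. The residual SD that returns exactly 0.80 at 0.27 is 0.27 × √184/(2 × 2.80) ≈ 0.65, and it is used below as a sensitivity value.

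**What the contrasts measure.** With weights in the order (AT+RT, AT, RT, BAT):
- interaction I = (1, −1, −1, 1)
- AT+RT against BAT = (1, 0, 0, −1)

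The sum of products is 1 + 0 + 0 − 1 = 0. With equal arms the two are orthogonal, so the interaction estimate says nothing about how far AT+RT exceeds BAT.

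**What the main effects do give.**
- M_AT = ½[(AT+RT − RT) + (AT − BAT)]
- M_RT = ½[(AT+RT − AT) + (RT − BAT)]
- M_AT + M_RT = AT+RT − BAT, whatever the interaction
- AT+RT − AT = M_RT + I/2, and AT+RT − RT = M_AT + I/2

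The two main effects therefore fix the contrast with BAT. Superiority over each single type needs the main effect and the interaction together.

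**Three illustrative sets of arm means.** All have the same main effects of 0.27; the arm means are assumptions, not the plan's.

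| AT | RT | AT+RT | M_AT = M_RT | Interaction | AT+RT minus each single type |
|---|---|---|---|---|---|
| 0.27 | 0.27 | 0.54 | 0.27 | 0 | 0.27 |
| 0.37 | 0.37 | 0.54 | 0.27 | −0.20 | 0.17 |
| 0.54 | 0.54 | 0.54 | 0.27 | −0.54 | 0 |

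In rows 1 and 2 the AT+RT arm is best, yet the interaction is zero or negative. In row 3 combining adds nothing, yet the main effects are unchanged.

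**Power in row 1.** SE of a two-arm contrast = 0.60 × √(2/46) = 0.125.
- AT+RT against BAT, 0.54: z = 4.32, power 0.99 (0.98 with SD 0.65).
- AT+RT against one single type, 0.27: z = 2.16, power 0.58 (0.51 with SD 0.65). Detectable at 0.80: 2.80 × 0.125 = 0.35 (0.38 with SD 0.65).
- AT+RT better than both single types: about 0.42, by simulation of the four arm means.
- Each main effect: 0.86; both: about 0.75.
- Interaction: true value 0, so its test rejects 5% of the time.

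**The case against.** **The planned comparisons already carry the answer.** Two of the three primary comparisons sum to AT+RT minus BAT, and the planned model, with AT, RT, AT × RT and their interactions with time, is saturated for the four arms at month 6. A reader might infer that the trial cannot answer its question about combined training. The documents do not support that: every arm contrast comes from the planned fit. Under additivity the main effects are even the stronger tests. What the objection does not cover is superiority over each single type, which the main effects alone cannot show (rows 1 and 3 of the table).

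**Additivity is not a planning assumption.** This stands. The plan gives 0.27 per main effect and says nothing of the true interaction, and it openly states that a large interaction is needed for 0.80 power. The scenarios only illustrate what the label does.

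**The comparison with BAT may be marginal.** BAT fills the sessions not given to AT or RT, so the Discussion's comparison with BAT can be read as the factorial main effect. This is fair. A reader might set the 0.58 for a single-arm contrast against the stated 0.80 as a power shortfall, but the plan claims 0.80 only for the effect of AT or RT and never for a single-arm contrast.

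**The expectation is one sentence in the Discussion, and follow-up contrasts can sit in an analysis plan not shown here.** Both are true, so the absence of those contrasts is not in itself the fault. An analysis plan would not, however, remove the definition in the primary objective. Nor does any passage say that a null interaction will be reported as no combined benefit; that is a risk created by the label, not a stated intention.

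**Conclusion.** The point holds as a mislabelled estimand, of moderate severity. The objective equates the combined effect with the interaction, and the three primary comparisons include no direct test that the AT+RT arm improves most. With the plan's sample size and residual variance, and assuming additive effects of 0.27 each, a 0.54 advantage of AT+RT over BAT (direct power about 0.99) sits beside a so-called combined effect of zero. With partial overlap the labelled effect is negative although AT+RT is best. The algebra needs only equal arms; the power figures also rest on 46 completers per arm and a residual SD of 0.60, and change little at 0.65. No primary test, sample size or data collection is shown to be wrong.

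**What to change.** 1. In the objective, call AT × RT the interaction and describe it as departure from additivity.
2. Define the combined-training effect separately as the model-based month-6 contrasts AT+RT against BAT, AT+RT against AT and AT+RT against RT, each with a 95% CI.
3. Label these contrasts secondary or estimation only, so that they add no primary tests to an alpha that is already uncorrected.
4. State that the powered tests of AT and RT are marginal factorial effects, and align the Discussion's comparison with BAT to either these or the single-arm contrasts.
5. State that a null interaction is not evidence against a combined benefit.

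The cost is a change of wording and three contrasts from the model already planned, with no new data; it is best made before unblinding. The drawback is that the two contrasts with the single-type arms are imprecise (power about 0.58 at 0.27, detectable effect about 0.35), so they should be presented as estimates with intervals.

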## Methods

### Design and setting

We will conduct a single-blinded, superiority, 2×2 factorial-arm RCT in a research center (Vancouver, British Columbia, Canada) with 216 community-dwelling older adults with MCI, as determined by a baseline Montreal Cognitive Assessment (MoCA) score < 26/30, with subjective memory complaints (SMC), without significant functional impairment, and no dementia (Clinical Dementia Rating (CDR) < 1.0) [42, 43], aged 65 to 85 years, living in Metro Vancouver, BC, Canada. This study will include a 6-month intervention and a 12-month follow-up (i.e., 18 months from baseline; Fig. 1). There will be a dedicated research coordinator (non-blinded) and trained assessors (blinded). Standardized protocols will be developed, and study personnel will be trained by the research team. Assessments and exercise sessions will occur at a research laboratory on the Vancouver General Hospital campus, Vancouver, Canada.

